### **Trial registration**

The protocol has been registered in University hospital Medical Information Network Clinical Trials Registry (UMIN-CTR), with approval number UMIN000008934.

### **Protocol version**

Version number: 1.0. Version data: July 17th, 2012

Version number: 2.0. Version data: September 20th, 2013

Version number: 3.0. Version data: June 14th, 2017(Final version)

### **Funding**

This study is carried out as a project of the Tazuke-Kofukai medical research institute (No:H-252013), the Japan society of acupuncture and moxibustion (JSAM) (No: jsam201201) research grant, and Japan Agency for Medical Research and Development (AMED) Research Project for Improving Quality in Healthcare and Collecting Scientific Evidence on Integrative Medicine (No: 18lk0310045h0001).

### **Roles and responsibilities**

The protocol was designed by [name], [name], [name], [name] and [name]. The funder had no role in study design, collection, management, analysis, and interpretation of data; writing of the report; and the decision to submit the report for publication.

## 1. Title of the research

Effect of long term intervention with acupuncture on COPD: A randomized controlled trial.  
Long term COPD Acupuncture Trial (LCAT)

### 3. Trial registration

The protocol has been registered in University hospital Medical Information Network Clinical Trials Registry (UMIN-CTR), with approval number UMIN000008934.

### 4. Roles and responsibilities

The protocol was designed by [name], [name], and [name]. The funder had no role in study design, collection, management, analysis, and interpretation of data; writing of the report; and the decision to submit the report for publication.

### 5. Objectives and significance of the research

- Objectives of the research

Purpose of our clinical trial is to study effects of acupuncture treatment on COPD patients for one year and evaluate its clinical effects of alleviating dyspnea on exertion and improving QOL (Quality of Life) of the patients.

- Significance of the research

Chronic Obstructive Pulmonary Disease (COPD) impairs patients' activities in daily life, their quality of life (QOL) and social activities due to dyspnea on exertion. Its prevalence is estimated to reach 5.3 million in Japan.

Main treatments for COPD currently are pharmacotherapy, oxygen therapy, respiratory rehabilitation, and nutritional counselling, but these treatments are not for curing the disease but for controlling the symptoms. And although it is reported important to ameliorate Dyspnea on Exertion (DOE) and improve QOL in order to manage COPD for a long period of time, it cannot be easily done by the current limited methods. Therefore, we consider it is necessary to supplement the current treatment methods.

There are some clinical studies reported which used acupuncture for COPD. Our clinical study using acupuncture for patients with COPD, where we gave acupuncture treatment once a week for 10 weeks for 30 cases with matched pair control, found that the mean Borg scale score, which indicates degree of dyspnea on exertion after 6-minutes' walk, was 6.43 (SD 3.46) for control group, and 2.17 (SD 2.66) for acupuncture treatment group. Since this preceding study indicated a certain effectiveness of acupuncture treatment for DOE of COPD, we then implemented a randomized control trial (RCT) with 12 weeks intervention and found that the mean Borg scale score after 6-minutes' walk were 4.6 (SD 2.8) for placebo group (n=32) and 1.9 (SD 1.5) for acupuncture treatment group, i.e., a significant improvement in acupuncture treatment group was seen. This study also found that acupuncture treatment group showed significant improvements in QOL of COPD patients (St George's Respiratory Questionnaire) and in nutritional evaluation (Body mass index, Prealbumin). Also, regarding the safety of acupuncture treatment, previous studies have not found any harmful incidents which cause physical pain including pneumothorax or danger of life.

Although its safeness and short-term effect for COPD were found by these studies, in order to have acupuncture treatment set as one of the COPD treatment programs, we consider that it is necessary to evaluate its effects for the much longer time period. Since there has been no study considering long-term effects of acupuncture treatment on COPD, we plan to study effects of acupuncture treatment on COPD patients for one year and evaluate its clinical effects including QOL.

## **6. Method and time period of the research**

### **• Study Design**

This study is a multi-center study and will be conducted at 4 facilities in Osaka Prefecture. This study is planned according to the CONSORT (Consolidated Standards of Reporting. Trials) statement, SPIRIT (Standard Protocol Items: Recommendations for Interventional Trials) guideline, and STRICTA (STandards for Reporting Interventions in Clinical Trials of Acupuncture) guideline.

Randomized parallel-group comparison study

Acupuncture Group (AG): Usual care and acupuncture treatment

Usual care Group (UG): Usual care only

### **• Blinding**

The nature of the study does not allow patients and acupuncturists to be blinded. However, in this study, blinding will be performed on the doctors in charge, the data collectors (including the evaluator), the data inputters, and the statistical analysts. In addition, data collectors and data inputters will be implemented by independent persons who are not involved in this research.

At all facilities, acupuncture is conducted in completely private rooms, and measures are taken to prevent participants from meeting each other. Additionally, the acupuncture rooms are located in a separate building from the hospital to avoid contact between participants and medical personnel.

Study Schedule

Patients' entry period: From 15 January 2013 to 31 October 2018.

Patients' entry method

Recruitment of relevant patients by the physician in charge of outpatient treatment.

Period of intervention

Period of intervention for this study is one year (52 weeks) in maximum.

\* Principal investigator is instructing the attending physician not to change the medication during the study in both groups. If a patient's condition worsened and treatment required a drug change, the drug change is temporarily permitted; however, when the patient's condition became stable, the previous treatment is resumed. The clinical researcher writes down about the medication and other treatment conditions on the specified record cards, which are preserved.

### **• Protocol of the Study (Material A-1, A-2)**

Informed consent and entry evaluation (various tests) of the patients are obtained at the

master hospital (Kitano Hospital Respiratory Center) as below.

A. The physician in charge evaluates whether a COPD patient fulfills the selection criteria.  
(Baseline, -4 to -2 Weeks)

B. The physician in charge explains this clinical trial to the patient and confirms the patient's intention orally whether he/she is "willing" or "not willing" to participate in this clinical trial. When the patient is willing to participate, the physician in charge notifies the clinical researcher of the patient's willingness, and then the clinical researcher sets up a meeting with the patient at the master hospital to obtain informed consent on this clinical trial from the patient. If the patient shows again the intention of participation at the meeting, informed consent of the patient is confirmed by a letter of consent. (Baseline, -2 week)

(At this stage, it is explained that even if the patient wants to have acupuncture treatment, he/she may not be able to have it.)

C. For the patient whose letter of consent is completed, the physician in charge at the master hospital orders the following tests as the initial evaluation. (Baseline, 0 Week)

In that case, if the patient visits the master hospital for the first time, the patient has to be registered as the first visit patient and to have the examination by the physician in charge and various tests according to the instruction given by the physician in charge at the master hospital. The reason to have the patient registered is to be able to take action immediately to avoid risk in case of sudden change during examinations such as the 6 minutes-walk or the detailed respiratory function test.

1. Respiratory function test: A detailed respiratory function test, B respiratory resistance (Impulse Oscillation System)
2. Blood test

Note: In order to alleviate the burden on a patient, if the patient's condition is stable, data for the tests 1 and 2 obtained within 1 months can be used. SGRQ questionnaire

4. Exercise tolerance test (6-minute walk test such as, dyspnea on exertion [modified Borg Scale], walking distance, lowest SpO2, highest pulse and lower limb fatigue [modified Borg Scale] )
5. Test on respiratory muscle strength
6. Physical evaluation test (height, weight, upper arm circumference, triceps brachii muscle skinfold thickness, grasping power, thorax excursion)

\* The evaluators are conducted by inspectors who are not related to this study.

D. When the initial evaluation is completed, the clinical researcher registers the patient to the clinical trial and asks the allocation center (Kyoto university) to allocate the patient.

(Baseline 0 week)

After completing the allocation process, the clinical researcher informs the participants which group they have been assigned to.

E. COPD patients who are allocated to AG (group with intervention) visit once a week one of the acupuncture treatment facilities collaborating with this study [The Tazuke Kofukai Medical Research Institute, Research Division for Integrating Oriental and Western Medicine (Osaka city), Ikeoka Acupuncture and Moxibustion Clinic (Osaka city), or Toneyama National Hospital Respiratory Medicine, Acupuncture and Moxibustion Room (Toyonaka city)] for 48 times (one year (52 weeks)). For each treatment, the person in charge of acupuncture treatment describes the progress and medical regimen on the acupuncture treatment record cards. The regular periodical examination for COPD patients of both AG and UG is given on the date designated by the physician in charge.

F. Tests shown above for initial evaluation are also to be given or ordered after 12 weeks and one year (52 weeks).

- **Random allocation**

The allocation of the participants to study groups is carried out in a centralized manner by setting up the allocation center at Kyoto University. After the baseline assessment and stratification by the GOLD classification (II or III or IV)(Material B), an independent investigator randomly assigned eligible patients to the usual care group(UG) or the acupuncture group(AG) in a 1:1 ratio using a computer-generated random allocation sequence(Microsoft excel. Microsoft Co., Washington D.C.,U.S.A ) with permuted block design and a block size of four.

To maintain blinding in physician, outcome assessors, and statisticians, the allocation sequence was concealed until the end of the study.

Statistical analysis is done by the statistician under masking. The allocation is labeled as “A” or “B”, and after the allocation is notified, the acupuncturist will set either “A” as usual care and “B” as acupuncture or the other way around. The clinical researcher and acupuncturists shall not reveal the statistician in which group a patient is allocated from the onset of the trial until the final statistical analysis is reported. The blind to the attending physician should not tell the result of the assignment unless an adverse event occurs. Also, the patient must not inform the physician in charge of the allocation result.

- **Method of acupuncture treatment (Material C1, C2)**

Acupuncture treatments are performed once a week for 48 times during the one year (52 weeks). Method of acupuncture treatment utilizes the acupuncture points which are reported effective for COPD by prior researches.

Acupuncture needles and positions of acupuncture points to be used.

Acupuncture needles used are disposable needles (Seirin Co., Ltd), 30-40mm in length and 0.14-0.25mm in thickness. The WHO standardized acupuncture points used in this study are as follows: ① LU1 (Zhongfu), ② LU9 (Taiyuan), ③ CV4 (Guanyuan), ④ CV12 (Zhongwan), ⑤ CV17 (Zhanzhong), ⑥ LI18 (Futu), ⑦ KI3 (Taixi), ⑧ ST36 (Zusanli), ⑨ BL10 (Tianzhu), ⑩ BL13 (Feishu), ⑪ BL20 (Pishu), ⑫ BL23 (Shenshu). (See figures and tables at the end of this document)

After inserting an acupuncture needle into both sides acupuncture point and the patient feels the deqi, the needle is rotated in a direction for 3 minutes to keep the deqi.

This procedure is performed on all acupuncture points. Total treatment time is about 60 minutes.

Acupuncturists who participate in this study are required to hold a national license and possess a minimum of 10 years of clinical experience. In addition, they must attend a five-week intensive program on acupuncture as part of the study.

- Acupuncturists participating in the study must meet the acceptance criteria within five weeks of receiving weekly evaluations from their instructors.

The evaluation consists of five items, with five criteria.

These include: Q1 Correct location of acupuncture point, Q2 Appropriate order of needle insertion, Q3 Appropriate needle insertion technique, Q4 Correct needle rotation technique, and Q5 Appropriate deqi level.

- The evaluation criteria require a minimum total score of 20 points to pass. The criteria are rated on a scale of 1 to 5, where 1 means 'not at all appropriate,' 2 means 'slightly appropriate,' 3 means 'fairly appropriate,' 4 means 'very appropriate,' and 5 means 'extremely appropriate'.

To account for variations in technique among acupuncturists, practitioners will be assigned on a monthly rotation basis to patients in this study.

The drugs used for patients in both groups will remain unchanged throughout the study, except in cases where therapeutic drug changes are necessary due to exacerbation. However, patients will be instructed to resume the original drug as soon as their condition stabilizes.

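### Allocation is central and independent, but one fixed block size of four printed in the protocol makes up to a third of assignments predictable to the unblinded clinical researcher

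*Protocol*

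**What the plan says.** In Protocol section 6, Random allocation, assignment is "carried out in a centralized manner by setting up the allocation center at Kyoto University". After the baseline assessment, "an independent investigator randomly assigned eligible patients" to usual care "or the acupuncture group(AG) in a 1:1 ratio". The sequence uses "stratification by the GOLD classification (II or III or IV") and was generated "with permuted block design and a block size of four". No second block size is mentioned, and site is not a stratification factor. The sequence is said to be concealed to keep physicians, outcome assessors and statisticians blind. The clinical researcher and the acupuncturists are not on that list.

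In section 6, Protocol of the Study, consent is taken at one master hospital. Under step B, "the clinical researcher sets up a meeting with the patient at the master hospital to obtain informed consent". Under step D the same role registers the patient and requests the allocation, and then "the clinical researcher informs the participants which group they have been assigned to".

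The paragraph on masking the statistician adds that allocation is labelled A or B and that "after the allocation is notified, the acupuncturist will set either" letter to mean usual care and the other acupuncture. It does not say whether this is done once for the trial or for each patient.

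**The concern.** Central allocation hides the next assignment from view. It does not prevent someone from inferring that assignment when the block size is fixed and known and past assignments are visible. Here one role sees those assignments and also controls the consent meeting and the moment of registration. All consent is at one hospital and strata are not split by site, so that role can follow each stratum's sequence. GOLD stage II or above is an inclusion criterion (section 7) checked at weeks -4 to -2, so the stratum will usually be known by the consent meeting.

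At stake is whether the two arms are comparable at entry. If the timing of entry could follow the expected arm, the arms could differ in motivation or expectation. The ANCOVA adjusts for the baseline value and GOLD class. It would not correct an imbalance in such other features, and the primary outcome (SGRQ total) is patient-reported in a trial of 44.

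**Working it through.** **Inputs.** Block size 4, ratio 1:1 and three GOLD strata (Random allocation); 44 patients (Sample Size). The protocol gives no figure for predictability, so there is none to reproduce. It also does not give the split of the 44 over strata, so all splits are considered.

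**Complete blocks.** Write A for acupuncture and U for usual care (not the A/B labels). The six possible orders are AAUU, AUAU, AUUA, UAAU, UAUA and UUAA.

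- Assignments 1 and 2 are never forced.
- Assignment 3 is forced when the first two match (AAUU, UUAA): 2/6 = 1/3.
- Assignment 4 is always forced.
- Share known with certainty: (0 + 0 + 1/3 + 1)/4 = 1/3.
- Probability that the best guess is right, by position: 1/2, 2/3, 2/3, 1. The mean is 2.833/4 = 70.8%, against 50% with no information.

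**44 patients, last blocks possibly incomplete.** A stratum of n = 4q + r patients has on average 4q/3 forced assignments, plus 1/3 if r = 3.

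- Split 20/16/8 (all blocks complete): 11 blocks × 4/3 = 14.7 patients, or 33.3%.
- Split 15/15/14: 4.33 + 4.33 + 4 = 12.7 patients, or 28.8%.
- Over every split of 44 into three strata, these are the maximum and the minimum.

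**Effect of varying the block size.** Simulation with 4,000 repeats. Sizes are drawn with equal probability. The observer knows the possible sizes and all past assignments, but not the current size. Each cell gives the results for splits 20/16/8 and 15/15/14. The alternative sizes are assumptions, not protocol figures.

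| Block sizes | Certain | Best guess right |
|---|---|---|
| 4 only | 33.3% / 28.8% | 70.8% / 68.9% |
| 4 and 6 | 5.9% / 6.0% | 68.2% / 67.8% |
| 2, 4 and 6 | 3.6% / 3.5% | 69.5% / 68.9% |
| 2 and 4 | 10.1% / 10.1% | 71.7% / 70.9% |

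Varying the size removes most of the certainty but barely changes the best-guess rate. Mixing only 2 and 4 slightly raises that rate.

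**The A/B label.** The sentence stands between one saying that the statistician works masked and one forbidding staff to reveal groups to the statistician. The preceding text assigns patients directly to usual care or acupuncture, and step D has the patient told the group. A letter attached afterwards does not change the treatment. If it were set anew for each patient, the letters would not consistently identify an arm and the masked analysis would lose its meaning. A code set once is therefore the sensible reading.

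**The case against.** The protections are real. Allocation is external and follows screening, written consent and baseline tests. The physician who recruits and judges eligibility is meant to be blind, so the exposure is confined to the clinical researcher's consent and registration steps. A reader might infer that allocation is unprotected; the documents do not support that.

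Consent is at week -2 and allocation at week 0, so steering at consent means predicting about two weeks ahead. This weakens the concern only a little. Entry from 15 January 2013 to 31 October 2018 is about 69.5 months, and 69.5/44 is one patient per 1.6 months on average, so few others would usually enter the stratum in between.

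A reader might also infer that the block size was public during recruitment. That is not shown. The final version is dated June 2017, after entry had begun, and the document does not say who could read the block size or when.

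Finally, a literal reading of the A/B sentence might suggest that the acupuncturist chooses who is treated, or that it contradicts assignment by an independent investigator. In context it does neither. What stands is that an unblinded treating role sets the statistician's code, after notification, in an unclear sentence.

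**Conclusion.** The point holds as partial predictability: about 29% to 33% of assignments (13 to 15 of 44) could be known in advance. One third is the upper bound. The range assumes someone who knows the block size, the stratum and every earlier allocation in that stratum, and that the clinical researcher's role is held by one person or by people who share records. It measures opportunity. It does not show that any patient's entry was steered, and baseline value and GOLD class are adjusted for in any case. The label wording is a separate, lesser matter of who holds the mask. Overall this is a cheap and worthwhile improvement, not a defect that invalidates the design.

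**What to change.** 1. For patients still to be allocated, have the allocation centre draw block sizes of 4 and 6 at random within GOLD stratum. Certain assignments fall to about 6%, or 2 to 3 of 44 (0.06 × 44 = 2.6).
2. Move the block scheme from the protocol to a document held by the allocation centre, withheld from recruiting and treating staff until allocation ends. This is needed because the best-guess rate stays near 68% for anyone who knows the scheme.
3. Replace the sentence on the A/B label: the allocation centre sets the code once, before the first allocation, and seals it until the final analysis is reported. State that it is an analysis code only.
4. For patients already allocated, record who knew the block size and from when, and who set the letter code, when, and whether once or per patient. By the protocol's own entry dates, this may be the only step still open.

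The cost is a new sequence for any future patients and a few sentences. The downside is small: an unfinished block can leave a stratum out of balance by three patients with blocks of six, against two with blocks of four.

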## • Outcome Measures

### A. Primary outcome measure

QOL questionnaire: SGRQ (St. George's Respiratory Questionnaire) Total domain in Japanese version.

\*Main evaluate the difference one year (52 weeks) after the baseline.

\*The SGRQ assessment is obtained by patients' filling in the paper-format questionnaires in a hospital room where no research-related personnel around, and the questionnaires are

collected by hospital staff unrelated to the study.

## **B. Secondary outcome measures**

As for Secondary and other outcome measures, the following outcome were evaluated at baseline, 12 weeks, and one year (52 weeks) later.

- a: QOL questionnaire: SGRQ total domain difference 12 weeks after the baseline.
- b: QOL questionnaire: SGRQ domain other than Total domain (Symptom, Activity, Impact).
- c: The 6-minute walk test (6MWT) assesses dyspnea on exertion using the modified Borg Scale (Material D), walking distance, lowest oxygen saturation level, highest pulse count, and lower limb fatigue measured with the modified Borg Scale.

\*Evaluate the difference 12 weeks and one year (52 weeks) after the baseline.

## **C. Other outcome measures**

- a. Nutritional measures: ① BMI (Body Mass Index), ② serum prealbumin, ③ serum albumin, ④ hemoglobin, ⑤ Midupper Arm Circumference (MAC), ⑥ Triceps Skinfold thickness (TSF), ⑦ Arm Muscle Circumference (AMC), ⑧ Arm Muscle Area (AMA), ⑨ grasping power.

\* Skinfold thickness measures to assess changes in fat mass using Harpenden skinfold calipers (Holtain) according to its standard methodology. Measurement is performed on the non-dominant hand, and in the case of paralysis, on the non-paralyzed side. We evaluate the average value of the three measurements. The measurement of TSF performs as follows. Subjects are in a lateral decubitus position, the upper arm was flexed by 90 ° at the elbow joint, a mark was placed at the midpoint between the shoulder bladder projection and the ulnar olecranon projection, the skin 1 cm away from the mark was picked up to so that the fat layer is separated from the muscle, and we measure the thickness by sandwiching the marked part with a caliper. As for the measurement of SSF, with the patients in the lateral decubitus position, the same method as TSF is used at the portion of the shoulder blade lower corner. For MAC, the surroundings of the part mark for TSF is measure with a measuring tape. AMC and are calculate by this formula:  $[AMC(cm)=MAC-3.14 \times TSF(cm)]$  and  $[AMA(cm)=(MAC-3.14 \times TSF)2/4\pi]$ , respectively.

- b: MMRC (modified Medical Research Council) dyspnea scale (Material E)

- c: Frequency and severity of acute aggravation of COPD are evaluated by dedicated daily records. The diary will be self-filled and will be submitted to an independent evaluator after the study period.

Contents of daily records \* Definition and Evaluation of acute aggravation: Severity scale (Material F)

Type 1 (sever): 3 major items are found

Type 2 (moderate): 2 major items are found

Type 3 (mild): 1major with any minor items are found

Major Items:

- (1) Obvious worsening of dyspnea, (2) Obvious increase of sputum purulence,
- (3) Obvious increase of sputum quantity

Minor Items:

- (1) Upper respiratory tract infection lasting more than 5 days, (2) Fever without other obvious cause, (3) Increased wheezing,
- (4) Increased cough, (5) Respiratory rate or heart rate increased more than 20%.

In addition, we evaluate the number of unscheduled outpatient visits and hospitalizations associated with exacerbation of COPD.

\* Evaluation of Severity scale is recorded on the specified evaluation table (daily record).

d. To evaluate QOL, CAT(COPD Assessment Test) Japanese version is used. The CAT, a disease-specific health status questionnaire, provides a measure of disease severity from the patient's perspective. It contains 8 questions (cough, phlegm, chest tightness, breathlessness, activities, confidence, sleep, and energy) that pertain to a patient's COPD symptom burden. Each question consists of a 6-point differential scale, and the final score is between 0 and 40.

e. BODE index is calculated. Prognosis outcome measurement is the BODE index, which is a multidimensional index that includes four factors that predict the risk of death: BMI (B); degree of air flow obstruction (O); functional dyspnea (D); and exercise capacity (E), assessed by the 6MWD.

f. Thorax excursion; Evaluation of thorax mobility was made by measuring the difference of the girth of the chest between the RV level and TLC level on the basis of the fourth intercostal using a tape measure.

g. Precision Respiratory function test: lung volume and its subdivision, flow volume curve, residual volume, pulmonary diffusion capacity.

h. Respiratory resistance: Impulse Oscillation System (IOS) is used to evaluate the respiratory resistance.

\* IOS parameters are collect before conventional spirometry parameters using the MasterLab IOS System (Erich Jaeger, Würzburg, Germany). Calibration is performed using a single volume of air (3 L) at different flow rates and a reference resistance device (0.2 kPa/L/s). The patients wear a nose clip and a manufacturer-provided, oval, hard plastic mouthpiece to prevent the expired air from escaping. They are also requesting to

support their cheeks with their hands to decrease shunt compliance. Artifacts caused by coughing, breath-holding, swallowing, and vocalization are not included. A single, experienced, respiratory technician made all the IOS measurements. The parameters evaluated are resonant frequency (Fres), resistance at 5 Hz (R5), resistance at 20 Hz (R20), the difference between the resistance at 5 and 20 Hz (R5-R20), reactance at 5 Hz (X5), area of reactance (AX), and impedance at 5 Hz (Z5) as calculating by  $\sqrt{X5^2 + R5^2}$ .

i. Test on respiratory muscle strength: Maximum respiratory muscle strength at expiration and inhalation is evaluated by maximum mouth pressure.

\* The maximum inspiratory mouth pressure (MIP) and maximum expiratory mouth pressure (MEP) were measured using a standard mouthpiece and a device (Vitaropower KH115, Chest MI Co. Ltd., Tokyo, Japan) according to American Thoracic Society/European Respiratory Society).

j. Inflammatory biomarkers: Interleukin-6 (IL-6), Tumor Necrosis Factor- $\alpha$  (TNF- $\alpha$ ), and High sensitivity CRP are measured.

The reason of the measurement: In recent years, it has been reported that COPD is a chronic systemic inflammatory disease and that systematic inflammation leads to worsening of COPD and causes comorbidities. On the other hand, it has been reported that acupuncture has an anti-inflammatory effect, and our previous study found some improvements in inflammation biomarkers related to COPD.

\*Evaluate the difference 12 weeks and one year (52 weeks) after the baseline.

k. Patients' expectations for acupuncture

Expectations for acupuncture were evaluated on the following Six-level Likert scale. Evaluation is performed at the time of baseline evaluation after informed consent (conducted before allocation).

"0: I have no expectations, 1: I do not expect much, 2: Indifferent, 3: I'm expecting a little, 4: Have medium expectations, 5: I have high expectations"

\*Patients' expectations for acupuncture are assessed at baseline only.

\*All evaluations are carried out by independent evaluators not involved in the research.

